## Abstract

**Background:**

About one-third of patients experience postoperative ileus (POI) after abdominal surgery, which can cause various complications and has not been treated well in clinical practice. The comprehensive treatment offered by traditional Chinese medicine may be a good choice for promoting intestinal mobility. Therefore, the aim of this study protocol is to observe the effectiveness of acupuncture combined with auricular acupressure in decreasing the incidence and related symptoms of POI.

**Methods:**

This is a single-center, assessor-blinded, randomized controlled trial. A total of 160 participants are supposed to recruit at Shanghai Tenth People's Hospital and randomly divided into two parallel groups in a 1:1 ratio. The intervention group are planned to receive manual acupuncture combined with auricular acupressure, while the control group are planned to receive regular enhanced recovery after surgery treatment. The primary outcome is the time to first defecation and first flatus after surgery. The secondary outcomes include the length of postoperative hospital stay, intensity of postoperative abdominal pain and distension, severity of postoperative nausea and vomiting, time to tolerate diet, inflammatory index, and incidence of prolonged postoperative ileus.

**Discussion:**

The results of this research will provide substantial evidence regarding the efficacy of comprehensive traditional Chinese treatment, specifically auricular acupressure and manual acupuncture, in treating and preventing POI.

**Trial registration:**

ClinicalTrials.gov, Identifier: ChiCTR2300075983, registered on September 21, 2023.

## Background

Postoperative ileus (POI) is an inevitable complication after abdominal surgery, which reflects a deceleration or complete cessation of bowel movements (1). Patients may present with symptoms such as abdominal pain and distension, vomiting, anal defecation, and defecation disorders. Research shows that POI occurring within 3 days for laparoscopic surgery or occurring within 5 days for open surgery is considered physiological; however, if it continues beyond these time frames, it can be considered pathological (2). POI is closely linked with negative factors, including an extended hospital stay, a higher likelihood of hospital-acquired infections or venous thromboembolism, and an increased rate of 30-day readmissions (3–5). The incidence of pathological POI can reach up to 10%–30% (6, 7) in abdominal surgery, which has become a current topic of concern in clinics.

To reduce the occurrence of POI, the conception of the enhanced recovery after surgery (ERAS) protocol has been implemented throughout the perioperative period (8). Many strategies have been supposed to promote bowel movement after surgery; however, only a few of them show a beneficial effect, such as μ-opioid-receptor antagonists, non-steroidal anti-inflammatory drugs (NSAIDS), laparoscopic surgery, and mid-thoracic epidural anesthesia (9–11). More strategies are still under exploration.

The inflammatory phase induced by abdominal surgery greatly impacts gastrointestinal dynamics and is therefore regarded as the main period of clinical prevention and treatment of POI (12). Several systematic reviews of randomized controlled trials (RCTs) on the effect of acupuncture and related therapies on bowel function after surgery show that acupuncture has a positive effect on bowel movement, including improvement of first flatus, first defecation, and first bowel sound (13–15). Manual acupuncture (MA) studies have shown anti-inflammatory effects in the digestive system through vagus nerve activation, TLR4/MyD88/NF-κB signaling, macrophage polarization, the mitogen-activated protein kinase (MAPK) signaling pathway, and the cholinergic anti-inflammatory pathway (16–18), which can be considered as the possible mechanisms of acupuncture in the treatment of POI. Another study reveals that acupuncture of hindlimb regions inhibits the expression of GABAA receptor in DMV neurons, which excites the vagal nerve and, in turn, suppresses inflammation via activation of the α7nAChR-mediated JAK2/STAT3 signaling pathway of POI (19). Auricular acupressure (AA) is another popular complementary approach for postoperative gastrointestinal dysfunction in abdominal surgery, which is non-invasive and has been approved to decrease the incidence of postoperative constipation (20). In clinical practice, these two treatment methods are always combined for simultaneous use; however, few research studies have focused on the comprehensive effect of their combined application in the treatment of POI.

Hence, this single-center, randomized controlled trial is designed to observe the effectiveness of acupuncture combined with auricular acupressure in decreasing the incidence and related symptoms of POI.

## Study design

The single-center, controlled, assessor-blinded, randomized trial is being executed in Shanghai Tenth People's Hospital from July 2023 and will continue until June 2026. The protocol is described in accordance with the Consolidated Standards of Reporting Trials (CONSORT) (21) guidelines and the Standards for Reporting Interventions in Controlled Trials of Acupuncture (STRICTA) (22). The study is registered at the Chinese Clinical Trial Registry (Identifier: ChiCTR2300075983) and is approved by the Ethics Committee of Shanghai Tenth People's Hospital (No. SHSY-IEC-5.0/23K82/P01). A total of 160 participants with elective laparoscopic surgery will be randomly assigned into an intervention group and a control group with a ratio of 1:1. Details of trial design and analysis plans are presented in Figure 1 and Table 1.

**Figure 1 F1:**
[figure not shown]
Flowchart of research.

**Table 1 T1:** Details of the study period.

	Study period				
	Visit 1	Visit 2	Visit 3	Visit 4	Visit 5
Time node	−7 to 0 day	0 day	3 days before surgery	Day 1–3 after surgery	Discharged from the hospital
Enrollment					
Informed consent	●				
General information	●				
Medical history	●				
Randomization		●			
Intervention					
AA + MA					
ERAS					
Assessment					
First defecation				●	
First flatus				●	
Length of postoperative hospital stay					●
Intensity of abdominal pain and distension				●	●
Severity of PNOV				●	●
Time to tolerate diet				●	●
Inflammatory index		●		●	●
Incidence of PPOI					●
Safety observation			●	●	●
Adverse event record			●	●	●
Obedience evaluation					●

## Recruitment

Patients in the abdominal surgery department of Shanghai Tenth People's Hospital will be diagnosed by a surgeon. All eligible participants will be explained the trial in detail by researchers and will be required to sign informed consent prior to participation. They will also have the right to withdraw from the trial anytime.

## Eligibility criteria

### Inclusion criteria

(1)Age ranging from 18 to 80 years;(2)Having upper gastrointestinal disease who will receive elective laparoscopic surgery, including benign hepatobiliary diseases, pancreatic diseases, gastric diseases, and malignant non-metastatic tumors;(3)Willing to sign the informed consent form and participate in the clinical trial.

### Exclusion criteria

(1)A history of serious diseases such as cardiovascular, cerebrovascular, liver, kidney, hematopoietic, digestive system, or mental illness;(2)A history of surgery in the stomach or intestine;(3)Having taken drugs for inhibiting gastrointestinal motility for over 2 weeks in the last 3 months;(4)Having received preoperative chemotherapy or radiotherapy;(5)Having received relevant treatments that may influence the effect of the study;(6)Unable to understand and fill out the scales related to the research.

## Randomization and blinding

The randomized program is developed using the Statistical Package for Social Sciences (SPSS) Ver. 24.0 (IBM Inc., New York, USA), and the opaque random envelope is used by the assistant to achieve the allocation concealment. The block grouping method is used to achieve randomization and set the length of the block group as 4. The random envelope is marked with the serial number of the group, and the group number is printed on the envelope. The envelopes are sequentially opened according to the time sequence of the included cases, and the control group and the intervention group are divided according to the groups in the envelope.

The participants and the acupuncturist will not be blinded because of the specialization of acupuncture manipulation. However, the data analysis and efficacy assessment will be performed by the research assistant and blinded to decrease analysis bias.

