## Outcome measures

### Primary outcome measures

The primary outcomes are the time to first defecation and first flatus, which is regarded as a bowel function indicator. This time is calculated from the end of laparoscopic surgery and will be recorded by nurses with accuracy to the hour.

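### A fixed, published block length of 4 at one centre lets up to a third of allocations be foreseen, and the assessor-blinded label does not cover the nurse-recorded primary outcome

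*Protocol article*

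**What the plan says.** The Study design section of the protocol article describes the trial thus: "The single-center, controlled, assessor-blinded, randomized trial is being executed in Shanghai Tenth People's Hospital". Its 160 participants "will be randomly assigned into an intervention group and a control group with a ratio of 1:1".

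The Randomization and blinding section fixes the block length: "The block grouping method is used to achieve randomization and set the length of the block group as 4". No stratification is described. On concealment it says that "the opaque random envelope is used by the assistant to achieve the allocation concealment". It adds that "the group number is printed on the envelope", and the next sentence has patients assigned by the groups found inside the envelopes, which are opened in order of inclusion.

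On blinding, the same section says: "The participants and the acupuncturist will not be blinded because of the specialization of acupuncture manipulation". It then says that "the data analysis and efficacy assessment will be performed by the research assistant and blinded".

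Under Primary outcome measures, the times to first defecation and first flatus "will be recorded by nurses with accuracy to the hour". No blinding of these nurses is mentioned.

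**The concern.** There are two separate matters. Block length bears on allocation concealment. Who records the times bears on outcome assessment. Neither causes the other.

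**Concealment.** A block of 4 under 1:1 allocation holds two of each arm, so the end of every block follows from its beginning. Opaque envelopes do not prevent this, because the inference comes from allocations already made. Treatment is open to view: under Interventions, ear seeds are applied from 3 days before surgery, and needling is given daily after it. If a recruiter can foresee the next arm, the order in which patients enter can be steered. There is room for that. Surgery is elective, and the inclusion criteria run from benign hepatobiliary disease to gastric and pancreatic disease and non-metastatic malignancy.

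**Blinding of the primary outcome.** The Discussion relies on assessor blinding to limit bias where double blinding is hard, and there is no sham arm. Yet the primary times are recorded by staff who are not named as blinded, while blinded assessment is assigned to someone else. In the intervention group both treatments continue until first defecation, so the event being timed also ends treatment. A reader who takes the label at face value would credit the primary outcome with a protection that the text does not give it.

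**Working it through.** **Inputs.** Block length 4 and 1:1 allocation (Randomization and blinding; Study design). Total 160 (Study design), which is 160 / 4 = 40 full blocks. The article gives no figure for predictability, so there is none to reproduce.

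**Fixed blocks of 4.** The six equally likely sequences are AABB, BBAA, ABAB, ABBA, BAAB and BABA. Assume that the observer knows the block boundaries and all earlier allocations, and always guesses the arm with more places left (a coin toss when they are equal).

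| Place in block | Chance that the arm is already certain | Chance that the best guess is right |
|---|---|---|
| 1 | 0 | 1/2 |
| 2 | 0 | 2/3 |
| 3 | 1/3 (after AA or BB) | 1/3 × 1 + 2/3 × 1/2 = 2/3 |
| 4 | 1 | 1 |
| Sum | 4/3 | 17/6 |

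- Certain: (4/3) / 4 = 33.3%. Over 160 allocations: 160 × 0.3333 = 53.3.
- Best guess right: (17/6) / 4 = 70.8%. Over 160 allocations: 160 × 0.7083 = 113.3, against 80 by chance.

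**Randomly varying blocks.** Sizes were drawn with equal probability in a simulation of 160 allocations (1,500 runs). The observer knows the set of sizes and all earlier allocations, but not the size of the current block.

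| Block sizes | Certain | Best guess right |
|---|---|---|
| 4 only (exact) | 33.3% | 70.8% |
| 4 or 6 | about 5% | about 69% |
| 4, 6 or 8 | about 2% | about 68% |

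Varying the length removes most of the certainty and little of the general guessability.

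**What steering could do (illustration only).** Suppose that easier and harder operations differ by 6 to 12 h in time to first defecation. This range is an assumption; the article gives no such figure. If every certain place were steered and the other two thirds stayed balanced, the group difference would shift by one third of that: 6 / 3 = 2 h to 12 / 3 = 4 h. The difference assumed under Sample size calculation is 85.1 − 77.8 = 7.3 h. This is a ceiling, not a forecast.

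**Blinding, side by side.** The Abstract and Study design call the trial assessor-blinded. Randomization and blinding gives efficacy assessment to a blinded research assistant. Primary outcome measures gives the recording of the primary times to nurses and states no blinding for them. A research assistant who later handles a time already written down by someone aware of the arm does not make that time a blinded measurement.

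**The case against.** The figures of 33% and 71% hold only for someone who knows the block length, the block boundaries and every earlier allocation. The article does not say that any recruiter does. Participants know their own arm, acupuncturists treat one arm only, and the Recruitment section has researchers explain the trial. This stands: both figures are upper bounds. It does not remove the point, because the block length is published and at one centre such tracking is feasible. If the sequence were stratified, tracking would have to be done within strata; none is described.

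Varying the blocks barely lowers the 71%. This also stands, and the remedy should be presented as removing certainty.

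A reader might infer that the printed group number reveals the arm and so defeats the envelope. The text does not support that. The envelopes are opaque, the next sentence places the groups inside them, and the printed number may be a block or sequence label.

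A reader might also infer that the assistant who uses the envelopes is the blinded research assistant. The article neither says nor excludes this, and a condensed article may leave the separation of roles to the full protocol.

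That nurses can see seeds and needling is an inference from how treatment is given. The mismatch does not need it: they are simply not among those described as blinded.

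**Conclusion.** The point holds in two limited parts.

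1. With fixed, disclosed blocks of 4 at a single centre with visible treatment, up to one third of allocations (at most about 53 of 160) can be foreseen with certainty, and up to 71% guessed correctly. This assumes one sequence and full knowledge of earlier allocations and block boundaries; with partial knowledge the figures are lower. Concealment is not assured. The documents do not show that it has failed or that enrolment has been steered.

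2. As written, the assessor-blinded label does not cover the primary outcome, because nurses with no stated blinding record the times. This rests on the text alone and needs no calculation. It is a mismatch of description, not evidence that the times are biased.

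The envelope marking and the identity of the assistant are ambiguous wording to be clarified. Neither shows that concealment or blinding is broken.

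**What to change.** - **Sequence.** For patients not yet randomised, generate a new list with randomly varying block lengths, and keep the lengths from recruiting staff. Trial status reports that recruitment is under way and does not say how many patients remain, so the benefit applies to that remainder and not to all 160.
- **Primary outcome.** Use one identical time log in both arms. Describe the nurse-recorded times as unblinded, unless the nurses who keep the log are unaware of allocation.
- **Clarifications.** State that only a sequence number appears on the outside of the envelope, and that the assistant who opens envelopes is not the blinded assessor.

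**Cost.** A new list and new envelopes, and possibly the reassignment of one role; the sample size is unchanged. Possible imbalance rises slightly. The largest difference between arms within a block is half its length: 2 for a block of 4, 3 for 6 and 4 for 8, so 1 to 2 patients more if recruitment ends inside a block, and up to 2 more if the old list is left in mid-block. The blinding label becomes weaker, but accurate.

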## Interventions

### Intervention group: MA combined with AA

MA and auricular acupressure procedures of the intervention group will be administered by licensed acupuncturists with 5–12 years of education in acupuncture and at least 3 years of clinical experience. They will all undergo unified and standardized training before trial initiation.

The intervention group will accept AA at the small intestine (CO6), large intestine (CO7), abdomen (AH8), and sub-cortex (AT4) according to the *Nomenclature and Location of Auricular Points* (Table 2 and Figure 2). Vaccaria seeds (Wang-Bu-Liu-Xing) (40 mm × 40 mm) (Changshu Shenling Medical Products Factory Co., Ltd., Changshu, China) will be embedded on the surface of auricular points and maintained between the two treatments. Two ears will accept AA alternately once daily. Participants will be suggested to press each point gently for 1 min thrice daily. The treatment will start 3 days before elective laparoscopic surgery and continue until the first defecation after surgery.

**Table 2 T2:** Location of auricular acupoints.

Auricular acupoints	Locations
Small intestine (CO6)	At the intermediate 1/3 of the region between the helix crus and Line AB^a^
Large intestine (CO7)	At the anterior 1/3 of the region between the helix crus and Line AB
Abdomen (AH8)	On the upper 2/5 of the body of the antihelix crus
Sub-cortex (AT4)	On the medial side of the antitragus

Point A: At the medial edge of the helix at the junction between the middle and upper 1/3 of the line from the notch of the helix crus and the inferior edge of the inferior antihelix crus. Point B: At the junction of the middle and posterior 1/3 of the line extending from the end of the helix crus to Point D. Point D: At a level line drawn from the end of the helix crus crossing the concha edge of the antihelix.

^a^
Line AB: A curved line that extends from Point A to Point B and mirrors the inferior edge of the helix crus.

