## Discussion

Based on the conception of ERAS, the treatment is designed to start before surgery to reduce the incidence of POI, which happens to have the same view as traditional Chinese medicine, “treat before disease attacks.” In addition, the study also set the ERAS group as the contrast, which may relatively objectively assess the effectiveness and safety of the two treatments.

As acupuncture has been widely accepted and applied in various diseases worldwide, other traditional Chinese therapies can also be taken into consideration, such as auricular acupressure. Auricular acupressure is low-cost, non-invasive, and has been approved for effectiveness in the digestive system (34). In clinical treatment, these two therapies are always combined to treat digestive diseases; however, few research studies have focused on such comprehensive therapy. Therefore, this study is supposed to approve the comprehensive effect of manual acupuncture combined with auricular acupressure in treating postoperative ileus.

The limitation of the study is that due to the specialization of acupuncture manipulation, double-blindness is hard to perform, so assessor-blindness is designed to decrease bias, and we have not set the sham-acupuncture group for the consideration of acceptability of postoperative patients.

To summarize, this trial aims to investigate the efficacy and safety of manual acupuncture combined with auricular acupressure in improving the symptoms and reducing the incidence of postoperative ileus. The results will be revealed at the end of the study and are expected to provide an alternative treatment option for preoperative patients, as well as contribute to the development of enhanced recovery after surgery.

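### Ear seeds worn only in the intervention arm reveal the allocation at the day-1 bedside assessment, so assessor blinding is not secured as written for the judged secondary outcomes

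*Protocol article*

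**What the plan says.** The abstract states: "This is a single-center, assessor-blinded, randomized controlled trial". Under Randomization and blinding, the article concedes that "The participants and the acupuncturist will not be blinded because of the specialization of acupuncture manipulation", and then says that "the data analysis and efficacy assessment will be performed by the research assistant and blinded to decrease analysis bias". The Discussion presents this as the remedy for the missing double-blinding ("so assessor-blindness is designed to decrease bias") and adds that "we have not set the sham-acupuncture group for the consideration of acceptability of postoperative patients".

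The section on the intervention group describes the auricular treatment. Vaccaria seeds "will be embedded on the surface of auricular points and maintained between the two treatments". On frequency it says "Two ears will accept AA alternately once daily", and on duration "The treatment will start 3 days before elective laparoscopic surgery and continue until the first defecation after surgery". The section on the control group mentions no ear device, real or dummy. No section describes covering the ears, or an assessor who does not meet the patient.

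On timing, the outcome section sets abdominal pain and distension at one day after surgery and at discharge. Table 1 places pain, distension, nausea and vomiting, and diet at Visit 4 (days 1 to 3) and at Visit 5 (discharge). Prolonged ileus is placed at Visit 5 and is defined by symptoms beyond 96 h. The two primary times are recorded by nurses.

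**The concern.** The seeds are a visible sign worn by one arm only, for a period that includes the first postoperative assessment. The needles leave no comparable sign, because each session ends with their withdrawal after 20 minutes. Seeds on an ear therefore identify an intervention patient, and early after surgery bare ears identify a control.

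Assessor blinding is the one safeguard the article offers in place of participant blinding and a sham arm. If the assessor can read the arm, outcomes that need a judgement are open to expectation: the four-grade distension rating, whether diet is tolerated, and possibly the symptom-based diagnosis of prolonged ileus. Any leaning could not be told apart from a treatment effect.

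**Working it through.** **The plan's own figure.** The plan gives no figure for how long seeds are worn. It does give the distribution of the event that ends wear: time to first defecation, 77.8 ± 15.6 h (intervention) and 85.1 ± 13.35 h (control), under Sample size calculation. These values reproduce the stated sample size if the larger SD is used for both arms: n = 2 × (1.960 + 0.842)² × 15.6² / 7.3² ≈ 71.7, so 72 per group, and 72 / 0.90 = 80. The point here does not depend on the sample size.

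**Share still wearing seeds.** Let T be time to first defecation in the intervention arm, with wear ending at T. With a normal shape, P(T > t) = 1 − Φ((t − 77.8) / 15.6). As a check on the shape, a lognormal with the same mean and SD has log-SD √ln(1 + (15.6/77.8)²) = 0.199 and log-mean ln 77.8 − 0.199²/2 = 4.334.

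| Hours after surgery | (t − 77.8)/15.6 | Normal | Lognormal | Controls |
|---|---|---|---|---|
| 24 | −3.45 | 99.97% | >99.99% | 0% |
| 48 | −1.91 | 97.2% | 99.0% | 0% |
| 72 | −0.37 | 64.5% | 61.4% | 0% |
| 96 | 1.17 | 12.2% | 12.3% | 0% |

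**What bare ears tell the assessor.** With 1:1 allocation, the probability that a patient without seeds is a control is 1 / (1 + share of intervention patients without seeds). At 24 h this is 1 / 1.0003 = 99.97%, at 72 h 1 / 1.355 = 74%, and at 96 h 1 / 1.878 = 53%. Seeds, when present, always mean intervention. The arm is thus almost fully readable on day 1, partly readable on day 3, and hardly readable from bare ears by 96 h.

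**Which outcomes this touches.**
- *Distension grade:* fixed at day 1 and discharge. The day-1 rating is fully exposed if the assessor makes it.
- *Diet tolerance:* Visits 4 and 5, with no fixed day. Exposure depends on when tolerance is judged and by whom.
- *Prolonged ileus:* judged after 96 h, when about 12% still wear seeds. It is affected mainly if the same assessor remembers an earlier sighting.
- *Pain VAS and nausea/vomiting scale:* patients who cannot complete the scales are excluded, which implies self-completion. Any bias comes mainly from patients who know their arm.
- *Laboratory values and length of stay:* little affected by what an assessor sees.
- *Primary times:* recorded by nurses, and outside this point.

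**The case against.** The strongest reply is that this is a journal article. How assessors are kept blind is often left to the full protocol, which may describe covering or separate logistics. That stands as far as it goes: a reader might infer that the trial has no masking at all, and the article cannot show that. But the point is more than missing detail. The article states a safeguard and also a visible one-arm marker that defeats it if the text is followed, and nothing in the article reconciles the two. The Discussion admits the lack of double-blinding and of a sham arm, but not that the assessor could see the allocation.

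Several stronger readings are tempting but unsupported:
- *That assessor blinding fails for the whole trial.* The primary times are recorded by nurses, and laboratory values and length of stay leave little to judgement. The article also does not say who records distension, diet or prolonged ileus, so attributing them to the assistant is itself an inference.
- *That all Visit 4 scores are taken with seeds in place.* Near-complete exposure holds on day 1. By 72 h about a third of intervention patients (100 − 64.5 = 35.5%) no longer wear them.
- *That masking would protect the pain and nausea scores.* Covering ears does nothing about the patients' own knowledge.
- *That bedside unmasking carries into the analysis.* The article gives both tasks to the research assistant, but this may name a role rather than one person, and coded analysis may be arranged in documents not shown.
- *That the bias can be turned into a false-positive rate.* No document gives the size of any leaning, so such a rate would rest wholly on an assumed shift.

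**Conclusion.** The concern holds in a limited form. As written, an assessor at the bedside on day 1 can identify the arm of essentially every patient: about 99.97% of intervention patients wear seeds, against no controls. The intervention share falls to about 97% at 48 h, 64% at 72 h and 12% at 96 h. The outcomes at risk are judged secondary ones: chiefly day-1 distension and diet tolerance, and prolonged ileus only through an earlier sighting by the same assessor.

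This assumes that the pilot mean and SD carry over to the trial, that wear ends at first defecation, that the times are roughly normal (the lognormal check gives the same picture), that the assistant sees the patient in person, and that no masking exists beyond what the article describes. The size of any resulting bias cannot be estimated from the documents.

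**What to change.** Under Randomization and blinding, and in the Visit 4 and Visit 5 procedures, state that both ears are covered in the same way in every participant of both arms before the assessor enters. State also that the analysis is run from a file in which the arms are coded A and B.

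For patients already assessed without covering, or if covering is not feasible, word the assessor-blinded claim in the abstract and design statement so that it does not extend to distension, diet tolerance and prolonged ileus. If the full protocol already contains a masking step, one sentence describing it would settle the point.

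The cost is a small ward task at each assessment and a procedure note, with no extra patients or visits. The limit is that Trial status dates first enrolment to November 2023 and recruitment is under way. Covering therefore protects only patients still to be recruited, and the report should say which patients were assessed under which procedure.
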